### Outcomes

#### Primary endpoint

The primary endpoint is the difference in transferrin saturation (%) at visit 1 between the high-dose intravenous infusion and the oral iron supplement group

#### Secondary objectives

The secondary objectives are:Other parameters of iron metabolism, red blood cell count including the percentage of participants with a normal (gender-specific) haemoglobin at visit 1 (group comparison) and further parameters (e.g. phosphate)Symptoms including those of restless legs syndrome, quality of life, fatigueComparison of the two treatments regarding the incidence and severity of adverse events, tolerance, and compliance

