**Discussion:**

Iron supplementation administered intravenously in non-anaemic but iron-deficient blood donors could represent an effective strategy to protect blood donors from comorbidities related with iron deficiency and therefore improve blood donor wellbeing. Furthermore, iron supplementation will help to maintain an iron-replete blood donor pool.

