## Background

Iron deficiency is possibly the most prevalent nutritional deficiency worldwide, but guidelines for its diagnosis and treatment vary in their suggestions [1, 2]. The largest part of iron is bound to haemoglobin in red blood cells [1]. Each whole blood donation (plus additional samples for testing) causes an iron loss of 200 to 300 mg [3]. Therefore, iron deficiency is prevalent among healthy blood donors, who represent up to 2–3 % of the population [4–10]. Contributing risk factors for iron deficiency include donation frequency, low body weight, and female gender [6, 8, 9]. Traditionally, safety issues in transfusion medicine have been concentrating on product quality and patient safety. However, there is still room for optimizing donor care [11]. In Austria, the maximal annual donation frequency for whole blood donations is 4 times for premenopausal women, 5 times for postmenopausal women and 6 times for men. The maximal annual donation frequency for platelet apheresis is 26 times and for plasmapheresis 50 times [12]. Recently, it has been shown that without iron supplementation, whole blood donors do not recover their predonation hemoglobin and iron status within 6 months [13]. Iron depletion in blood donors has been recognized for decades [14], and anaemia is routinely assessed by point-of-care haemoglobin devices, but iron status is not. Therefore, non-anaemic iron-deficient donors may not be identified, as iron deficiency may lead to subtle and unspecific symptoms [15].

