### Aims and hypothesis of the study

This study will assess the efficacy, safety, and feasibility of intravenous infusion of high-dose iron in blood donors with iron deficiency by comparing intravenously administered ferric carboxymaltose with oral iron fumarate supplements.

Our hypothesis is that 1 g of intravenously infused ferric carboxymaltose will improve the iron status of blood donors with iron deficiency more efficiently compared to a comparable dose of oral iron supplements (10 g assuming a 10 % resorption rate, given over 8–12 weeks).

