### Study design

This is a prospective, randomised, clinical trial. The study population consists of healthy adults, including male and female whole blood and platelet apheresis donors with iron deficiency (ferritin ≤ 30 ng/ml).

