### Participants

#### Inclusion criteria

The inclusion criteria are as follows:Age ≥ 18 years and ≤ 65 yearsIron deficiency (ferritin ≤30 ng/ml at screening — usually before blood donation)Fulfilment of the Austrian criteria for blood donation

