### Screening

Typically after a regular whole blood or platelet apheresis donation, ferritin is measured from the remaining serum for routine infectious disease testing. The regular written informed consent for blood donation covers the additional ferritin analysis. Donors with a serum ferritin ≤30 ng/ml will then be invited by telephone to participate in the study.

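### The normal-haemoglobin endpoint at visit 1 takes no account of haemoglobin at visit 0, so it mixes donors who were corrected with donors who were never low; the abstract's non-anaemic wording is likewise not secured by the entry criteria

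*Protocol article*

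**What the plan says.** **Endpoint.** Secondary objectives places "the percentage of participants with a normal (gender-specific) haemoglobin at visit 1 (group comparison" within the red-cell parameters. It makes no reference to the participant's haemoglobin at visit 0.

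**Entry criteria.** Inclusion criteria lists an age range, ferritin ≤30 ng/ml and "Fulfilment of the Austrian criteria for blood donation". Neither that list nor Exclusion criteria states a haemoglobin value or names anaemia. Background notes that at donation "anaemia is routinely assessed by point-of-care haemoglobin devices, but iron status is not", so haemoglobin enters indirectly through donor eligibility.

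**Timing.** Under Screening, "Typically after a regular whole blood or platelet apheresis donation, ferritin is measured". Visit 0, where randomisation takes place, is 4–6 weeks after donation. Background gives 2–3 months as the minimal interval between whole blood donations, and reports that "without iron supplementation, whole blood donors do not recover their predonation hemoglobin and iron status within 6 months".

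**Population wording.** The Discussion paragraph of the Abstract says: "Iron supplementation administered intravenously in non-anaemic but iron-deficient blood donors could represent an effective strategy". The hypothesis is that intravenous iron "will improve the iron status of blood donors with iron deficiency more efficiently", and Study design describes healthy adults "including male and female whole blood and platelet apheresis donors with iron deficiency". Neither of these mentions anaemia.

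**The concern.** A whole-blood donor at visit 0 is still inside the minimal donation interval. For such a donor the eligibility criterion is most naturally read at the screening donation, before that unit of blood was lost. On the protocol's own background, haemoglobin may not have returned to its earlier level by visit 0, so some participants may be below the gender-specific limit when randomised.

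Two things follow. First, the percentage normal at visit 1 combines two different outcomes: correction in donors who were low, and staying normal in donors who were not. If few were low, a real difference in correction is compressed into a small difference near the top of the scale, and a non-significant result could be misread as equal correction. Second, if an appreciable share were low, a conclusion worded for non-anaemic donors would not describe everyone analysed.

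**Working it through.** **Inputs from the protocol.** 86 participants per group and a two-sided 0.05 level (Sample size justification); 1:1 allocation stratified by gender (Randomization procedure). The 86 was derived for transferrin saturation. The protocol states no sample size or power for haemoglobin, so there is no planned figure to reproduce here.

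**Inputs assumed.** The protocol gives neither the share low at visit 0 nor the expected haemoglobin response, so ranges are used.
- f, the share below the gender-specific limit at visit 0: 5, 10, 20 or 30 %, equal in both arms.
- c, the share of those corrected by visit 1: 80 % (intravenous) and 50 % (oral). An alternative uses 100 % and 50 %.
- Donors normal at visit 0 stay normal.

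**Step 1: what the endpoint measures.**

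P(normal at visit 1) = 1 − f × (1 − c)

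Difference between arms = f × (c_IV − c_oral), which cannot exceed f.

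Example with f = 0.10: intravenous 1 − 0.10 × 0.20 = 98 %; oral 1 − 0.10 × 0.50 = 95 %. A 30-point difference in correction appears as 0.10 × 30 = 3 points.

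**Step 2: power of the endpoint as written** (exact power of Fisher's test, 86 per arm).

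| Low at visit 0 | IV v oral normal at visit 1 (80 v 50 % corrected) | Difference | Power | Power if 100 v 50 % corrected |
|---|---|---|---|---|
| 5 % | 99 v 97.5 % | 1.5 points | 1 % | 2 % |
| 10 % | 98 v 95 % | 3 points | 7 % | 26 % |
| 20 % | 96 v 90 % | 6 points | 24 % | 87 % |
| 30 % | 94 v 85 % | 9 points | 41 % | 99 % |

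**Step 3: the same question asked only of those low at visit 0.** The expected number per arm is 86 × f, that is 4.3, 8.6, 17.2 and 25.8, or about 4, 9, 17 and 26. Fisher's exact power for 80 % v 50 % at those sizes is about 3, 15, 32 and 54 %.

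Conditioning on visit 0 status raises power in each case and estimates correction directly. Power stays modest because few donors are low.

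**Step 4: the wording.** The Abstract's Discussion speaks of non-anaemic donors. Aims and hypothesis and Study design speak of iron-deficient donors. The stated criteria match the second description and do not guarantee the first.

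**The case against.** Several points on the other side stand.

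- **Dilution is not bias.** Allocation is random, so never-low donors are balanced between arms in expectation. The proportion normal at follow-up is a legitimate outcome, and it also captures donors who become low, which the model above sets to zero.
- **Continuous haemoglobin appears to be covered.** The percentage is one item within the red-cell parameters, and Statistical procedures provides for analysis of all secondary outcomes, with t or rank tests for laboratory results. The percentage is not the only view of haemoglobin.
- **Much of the low power comes from small numbers.** Step 3 shows that changing the definition helps only to a limited extent.
- **A condensed article** may leave baseline adjustment to the full protocol or analysis plan.

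A reader might also infer more than the documents support:

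- *That the endpoint sits at its ceiling and would show no difference.* This depends on an unstated baseline share. With 20–30 % low and intravenous iron correcting all, power is 87–99 %.
- *That haemoglobin plays no part in eligibility.* Donor eligibility is an indirect gate, and inclusion criteria are checked at visit 0. The haemoglobin component could have been applied then, although the text does not say so.
- *That many participants must be anaemic.* Haemoglobin not yet back to its predonation level is not the same as haemoglobin below the normal limit. The argument also concerns whole-blood donors; the Abstract equates ten apheresis donations with one whole blood donation in iron loss.
- *That the trial is designed to speak only for non-anaemic donors.* That wording is one conditional sentence in the Abstract. Background and the main Discussion mention iron deficiency without anaemia as motivation, but no objective or endpoint is restricted to it.

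**Conclusion.** The point holds in a limited form. As worded, the percentage normal at visit 1 does not separate correction from never having been low, whatever the baseline share. If no one becomes newly low, the difference that correction can produce is capped at the share low at visit 0. With 80 % v 50 % correction and 86 per arm, a 30-point difference shrinks to 1.5–9 points, with power of about 1–41 % over a baseline share of 5–30 %. These figures rest on assumed inputs, and power improves sharply if intravenous iron corrects nearly all.

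The non-anaemic phrase in the Abstract is not secured by the entry criteria, whereas the aim and design are worded consistently with them. The effect is on the reading of one secondary endpoint and of one sentence about the population. It is a minor-to-moderate point.

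**What to change.** Methods of procedure reports that all participants have been included, so the change concerns analysis and reporting only.

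1. Confirm that haemoglobin was measured in the visit 0 sample. Blood samples describes the draw but does not list its parameters.
2. Report, by arm, how many participants were below and how many within the gender-specific limit at visit 0.
3. Report the percentage normal at visit 1 separately for those two groups, each with a confidence interval for the arm difference. Both groups are defined before treatment, so the comparison within each is still between randomised arms.
4. Analyse continuous haemoglobin at visit 1 with visit 0 haemoglobin taken into account, for example as a covariate.
5. Describe the population as iron-deficient donors with or without anaemia, unless the primary comparison is also shown in those with normal haemoglobin at visit 0.

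If visit 0 haemoglobin was measured, the cost is endpoint wording and a few analyses on existing data. The downside is that the low-haemoglobin group may hold only about 4–26 per arm over the range considered, with power of about 3–54 % on the 80 % v 50 % assumption. Its result should be read from the confidence interval, and a non-significant test should not be taken as evidence of equal correction.

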### Methods of procedure

A flow chart of the study procedure is given in Fig. 1. The total study duration for each patient will be 8–12 weeks. Based on previous experiences in the recruitment of blood donors for observational studies, we aim to include two study participants per week. Thus, the total recruitment period is estimated to last for 21–24 months and the total active study duration will be 26 months. Recruitment started in June 2014 and was completed in June 2016. At the time of revision, all 176 participants (172 according to the sample size calculation plus 4 dropouts) have been included.

**Fig. 1 Fig1:**
[figure not shown]
Study flow chart

### Study duration for the individual participant

The active treatment period for each participant is 8–12 weeks.

### Screening

Typically after a regular whole blood or platelet apheresis donation, ferritin is measured from the remaining serum for routine infectious disease testing. The regular written informed consent for blood donation covers the additional ferritin analysis. Donors with a serum ferritin ≤30 ng/ml will then be invited by telephone to participate in the study.

### Visit 0 including randomization procedure (4–6 weeks after blood donation)

Donors willing to participate are requested to visit the Apheresis Unit of the Department of Blood Group Serology and Transfusion Medicine. After giving written informed consent, checking inclusion/exclusion criteria and performing a urine pregnancy test in premenopausal females, a case report form (CRF) is filled out by the donor.

The CRF includes questions on the following aspects:History of blood donation (total number, time)History of anaemiaSymptoms of fatigueSubjective physical and cognitive performance including self-reported physical activity and hours worked per weekSymptoms of depression or lethargyTrophic changes of fingernails or hairFatigue induced by blood donationSymptoms of restless legs syndrome

#### Randomization procedure

Each participant will be randomized in a 1:1 ratio (stratified by gender) to either high-dose parenterally infused iron or oral iron supplements using a web-based randomisation tool (http://www.randomizer.at). Good clinical practice (GCP) compliance of this software was confirmed by the Austrian Agency for Health and Food Safety (AGES).

#### Blood samples

A blood sample (~30 ml) is drawn from all participants, in case of randomisation to parenterally infused iron from a venous access placed for the application of the intravenously administered iron. Some parameters may be measured after the end of the study from frozen blood specimens stored at −70 °C.

#### Faecal occult blood tests

To assess occult gastrointestinal bleeding, all participants are asked to perform three faecal occult blood tests at home in the time between visit 0 and visit 1.

#### Medication

According to the randomization, either 100 tablets of oral iron supplements are handed out to the participant or iron is administered intravenously by the study investigators in the presence of a nurse.

For oral iron supplements, all participants receive an exact schedule for tablet intake together with clear instructions according to the package leaflet: we suggest to take 10 tablets per week (3 days 2 tablets, 4 days 1 tablet) and to take the tablets with orange juice.

Iron is administered intravenously to the participants in a bed in a separate room of the Apheresis Unit of the University Clinic of Blood Group Serology and Transfusion Medicine. Iron is infused intravenously over 30 minutes or more over a dedicated peripheral line. A standard operating procedure involving the resuscitation outreach team of the Department of Anesthesiology has been developed, and basic emergency equipment is available at all times.

### Visit 1 (8–12 weeks after visit 0)

A treatment period of 8–12 weeks is chosen because the administration of 8–13 doses of 100 mg iron in one week is feasible and it also matches the typical donation interval. Furthermore, serum ferritin levels are falsely high when analysed ≤6 weeks after intravenous infusion of iron.

A CRF including assessment of compliance is completed by the donor, and a blood sample (~30 ml) is drawn. All results are summarized in a written report for the study participants and sent by regular mail.

The CRF at visit 1 will additionally include questions on the following aspects:Information on any relevant adverse events, serious adverse events and adverse drug reactionsCompliance with oral study medication intake (self-reported; the participants are also asked to bring back all leftover medication)

### Statistical aspects

#### Sample size justification

The sample size calculation was performed by the Department of Medical Informatics, Statistics and Documentation of the Medical University of Graz. Using a two-group *t* test with a 0.05 two-sided significance level, a sample size of 86 participants in each group will have 90 % power to detect a difference in mean of 8 % in transferrin saturation (estimating a post-treatment transferrin saturation of 28 % and 20 % in the high-dose intravenous iron group and oral iron group, respectively, based on results by a similar treatment regimen in otherwise healthy women with postpartum anaemia [34]). Allowing for a dropout of 14 %, originally 200 participants were planned to be enrolled in the study. As the actual dropout rate was substantially lower (<3 %), the study will be terminated after complete study participation of 172 participants plus the number of dropouts.

#### Statistical procedures

Statistical analyses of the results will be performed using the intention-to-treat and the per-protocol principles. All study participants who are randomised and included into the study will be analysed whether they take their study medication for the entire term (oral iron) or not or whether or not they miss the follow-up visit (visit 1). All primary and secondary outcome measures will be analysed and checked for normal distribution of the results. If there is a normal distribution of laboratory results, they will be analysed by the two-sided *t* test; if there is not a normal distribution they will be analysed by non-parametric tests like the Wilcoxon test for related samples or the Mann-Whitney U test for comparison of independent samples. The significance level will be set to *p* < 0.05. Data will be presented as mean ± standard deviation or median (interquartile ranges) as appropriate. For missing data, no imputation will be performed. A statistical evaluation will be performed using the software program SPSS for Windows (IBM SPSS Inc., Chicago, IL, USA).

A predefined subgroup analysis will separately analyse participants with a baseline ferritin of ≤15 ng/ml. The Department of Blood Group Serology and Transfusion Medicine, Medical University of Graz, will maintain responsibility for the final trial dataset.

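### The plan promises to analyse participants who miss visit 1 but rules out imputation, so the primary intention-to-treat result can only be an available-case analysis as randomised

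*Protocol article*

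**What the plan says.** All references are to the protocol article.

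- **Analysis principle** (Statistical procedures): "Statistical analyses of the results will be performed using the intention-to-treat and the per-protocol principles".
- **Who is included** (same section): "All study participants who are randomised and included into the study will be analysed", whether or not oral iron is taken for the full term, "or whether or not they miss the follow-up visit (visit 1").
- **Missing data** (same section): "For missing data, no imputation will be performed".
- **Test** (same section): a two-sided t test if the results are normally distributed, otherwise a non-parametric test, which between groups is the "Mann-Whitney U test for comparison of independent samples".
- **Endpoint** (Primary endpoint): "The primary endpoint is the difference in transferrin saturation (%) at visit 1 between the high-dose intravenous infusion and the oral iron supplement group".
- **Numbers** (Methods of procedure): 176 participants enrolled, described as "172 according to the sample size calculation plus 4 dropouts". The Sample size justification ends the study once 172 have participated completely, with dropouts counted on top.

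**The concern.** Someone who misses visit 1 has no value of the primary endpoint. Neither named test can use that person without a substituted value, and substitution is ruled out. The inclusion sentence is therefore unachievable for the primary comparison.

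At stake is the accuracy of the stated analysis set. A report that followed this wording would describe an analysis of everyone randomised while the primary comparison covered only those who returned. An available-case comparison is unbiased only if, within each arm, those who did not return resemble those who did. The plan neither states that assumption nor provides a check on it.

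**Working it through.** **1. Can both statements hold?** The primary endpoint is defined at visit 1. The section on visit 1 describes the only blood sample after treatment, so no other post-treatment value can stand in. The t test and the Mann-Whitney test each compare observed values in two independent groups. A participant without a visit-1 value contributes to neither, so with imputation excluded the analysis set is those who have one.

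**2. The plan's own figures.**
- Enrolment: 172/(1 − 0.14) = 200, as stated.
- Final count: 172 + 4 = 176, as stated. Dropout is 4/176 = 2.3 %, consistent with the stated rate below 3 %.
- SD: not stated. With 86 per group, 90 % power, a "0.05 two-sided significance level" and a difference of 28 − 20 = 8 points, the normal approximation gives SD = 8 × √(86/2)/(1.960 + 1.282) = 16.2. The t test gives about 16.1. I use 16 below as an assumption.

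**3. Effect on power** (t test, SD 16, difference 8).

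| Participants with a visit-1 value | Power |
|---|---|
| 88 + 88 (all 176) | 0.910 |
| 86 + 86 (172) | 0.903 |
| 88 + 84 (172, all four dropouts in one arm) | 0.903 |

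**4. Effect on the estimate.** If m of n participants in an arm are missing and their mean differs from the observed mean by δ, the full-arm mean differs from the observed mean by (m/n) × δ. I assume 88 per arm and that all four dropouts lack a visit-1 value.
- All four in the intravenous arm, at the planned oral mean of 20: (84 × 28 + 4 × 20)/88 − 20 = 7.64, a shift of 0.36.
- Two per arm, each at the other arm's planned mean: (86 × 28 + 2 × 20)/88 − (86 × 20 + 2 × 28)/88 = 27.82 − 20.18 = 7.64, again a shift of 0.36.
- All four in one arm, one SD from that arm's observed mean: 4 × 16/88 = 0.73.

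For contrast, at the 14 % dropout first planned for (14 of 100 per arm), the same kind of assumption matters more. With the missing intravenous participants at 20, the difference is (86 × 28 + 14 × 20)/100 − 20 = 6.88. With both arms exchanged, it is 26.88 − 21.12 = 5.76. The low dropout is what keeps the issue small.

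**5. Would a longitudinal model bring these participants in?** Take visit-0 and visit-1 values as jointly normal with a common baseline mean. The likelihood then factors into the baseline distribution and the regression of visit 1 on baseline and arm. Because the baseline mean is shared, the visit-1 treatment contrast equals the arm coefficient in that regression, which is estimated only from people with a visit-1 value. A participant with baseline alone informs the baseline mean and variance, not the contrast. With one post-treatment measurement, the model gives the same treatment estimate as ANCOVA on those with visit-1 data.

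**The case against.** The best defence is that intention-to-treat without imputation is common shorthand for all available data, analysed as randomised. The article is also open about numbers: it sizes the trial on 172 full participants and lists dropouts separately. Participants who miss visit 1 can still count for safety, because adverse events may be reported by telephone, so the inclusive sentence is not empty for every outcome. A separate analysis plan may add detail.

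Much of this stands, and it limits the point to the primary comparison and other visit-1 measurements. It does not remove the conflict, because the text expressly includes those who miss visit 1. An analysis plan could not honour both sentences with the named tests; one would have to change.

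The documents do not support several stronger readings that a reader might infer:
- **That this is a treatment-completer analysis, in effect per-protocol.** People who stop their tablets but attend visit 1 remain in the analysis as randomised.
- **That the result is biased in favour of oral iron.** The Background says gastrointestinal side effects are less frequent with intravenous iron, so intolerance could drive dropout from the oral arm. But the arms of the four dropouts, their reasons, and whether all four lack a visit-1 value are not given.
- **That naming two analysis principles without ranking them is an error, or that per-protocol exclusions can arise only in the oral arm.** Ranking and set definitions are commonly left to documents not shown here. No per-protocol definition is given, and the secondary objectives compare compliance between both treatments.

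**Conclusion.** The point holds as a minor correction. The primary intention-to-treat analysis, as described, cannot include participants who miss visit 1. It will be an available-case analysis as randomised, of about 172 of 176 if all four dropouts lack a visit-1 value.

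The likely numerical effect is small: about 0.4 to 0.7 points against 8, and power of 0.903 rather than 0.910. These figures assume an SD of 16, 88 per arm and the departures shown for the missing values. One SD is an illustration, not a bound. Nothing in the documents suggests that the primary conclusion is at risk. What is wrong is the stated property of the analysis.

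**What to change.** 1. **Restate the set.** Define the primary analysis set as all randomised participants with a visit-1 transferrin saturation value, analysed in the arm to which they were randomised. Report by arm how many are absent and why.
2. **Adjust the comparison.** Use ANCOVA with visit-0 transferrin saturation and gender, the stratification factor. This should gain precision, by an amount that depends on the unreported correlation between visits. It also relaxes the missing-data assumption to missing at random given arm, baseline and gender. It presumes that transferrin saturation is measured in the visit-0 sample and that this sample precedes the infusion. The article describes the sample for all participants but does not itemise its assays.
3. **Replace the blanket no-imputation rule.** Add a tipping-point or best/worst-case sensitivity analysis that includes everyone randomised. With about four missing values this is quick.
4. **Do not offer a constrained longitudinal model as the remedy.** It would not bring participants without visit-1 data into the treatment contrast.

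The cost is a few lines of analysis-plan wording, one standard model and a short sensitivity table, with no new data collection provided the visit-0 assay is available. Recruitment is complete, so the change should be dated and recorded before the arms are compared.

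### The unadjusted primary comparison is valid but omits the gender stratum and visit-0 transferrin saturation, forgoing precision of unknown and possibly small size

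*Protocol article*

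**What the plan says.** All places are in the protocol article.

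- **Primary endpoint:** "The primary endpoint is the difference in transferrin saturation (%) at visit 1 between the high-dose intravenous infusion and the oral iron supplement group". This is the post-treatment value, not a change from baseline.
- **Statistical procedures:** "If there is a normal distribution of laboratory results, they will be analysed by the two-sided" t test. If the distribution is not normal, the independent-groups option is the "Mann-Whitney U test for comparison of independent samples".
- **Sample size justification:** a two-group t test at a "0.05 two-sided significance level", 86 per group, 90 % power, expected means of 28 % and 20 %. Planned analysis and sample size therefore agree.
- **Randomization procedure:** "Each participant will be randomized in a 1:1 ratio (stratified by gender".
- **Blood samples (visit 0):** a sample of about 30 ml "is drawn from all participants, in case of randomisation to parenterally infused iron from a venous access". The analytes are not listed, and some may be measured later from frozen specimens.

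Neither gender nor visit-0 transferrin saturation enters the primary comparison anywhere in the article.

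**The concern.** A factor used to stratify randomisation is normally carried into the analysis. If it predicts the outcome and is left out, the variance between strata stays in the error term, although stratification has already removed that variation from the difference between arms. The standard error is then somewhat too large. Gender is a plausible predictor here: the Background names female gender as a risk factor for iron deficiency, and the section on gender relevance enlarges on it.

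Similarly, a baseline measurement of the outcome that correlates with the visit-1 value explains part of the outcome variance. Leaving it out gives a wider confidence interval than the same participants could support. Recruitment is reported complete at 176, after the target was cut from 200, so the analysis is the main remaining source of precision.

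**Working it through.** **Inputs from the article.** 86 per group; difference 28 − 20 = 8 points; two-sided alpha 0.05; power 90 %; planned dropout 14 %.

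**Inputs not given, so assumed.** The SD, back-solved below. The correlation r between visit-1 transferrin saturation and the covariates, taken as 0.2 to 0.6. If both visit-0 value and gender are in the model, r is their multiple correlation with the outcome, so gender is already inside r and is not a further gain.

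**1. The plan's own figure.** Without an SD, 86 cannot be checked independently, but the SD it implies can be found. By the normal approximation:

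SD = 8 / [√(2/86) × (1.960 + 1.282)] = 8 / (0.1525 × 3.242) ≈ 16.2.

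The exact noncentral-t calculation gives 16.09. A round SD of 16 returns 86 per group (power 90.3 %), so the figure is coherent with an SD near 16. The enrolment target also reproduces: 172 / (1 − 0.14) = 200.

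**2. Effect of adjustment.** Residual SD = 16.09 × √(1 − r²). Power is exact t with 86 per group. CI half-width = t × residual SD × √(2/86).

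| r (assumed) | Residual SD | Power | n per group for 90 % | 95 % CI half-width (points) |
|---|---|---|---|---|
| 0 (as planned) | 16.09 | 90.0 % | 86 | 4.84 |
| 0.2 | 15.77 | 91.1 % | 83 | 4.75 |
| 0.3 | 15.35 | 92.5 % | 79 | 4.62 |
| 0.4 | 14.75 | 94.3 % | 73 | 4.44 |
| 0.5 | 13.94 | 96.3 % | 65 | 4.20 |
| 0.6 | 12.87 | 98.2 % | 56 | 3.88 |

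**3. Gender alone.** Simulation with 20,000 runs, 172 participants, balanced strata, about 60 % women (assumed) and an SD of 16.09 within each gender. The gender difference in the outcome is also assumed.

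| Gender difference (points) | Type I error, unadjusted | Type I error, adjusted | Power, unadjusted | Power, adjusted |
|---|---|---|---|---|
| 4 | 4.9 % | 5.1 % | 89.9 % | 90.2 % |
| 8 | 4.3 % | 5.0 % | 89.1 % | 90.1 % |
| 12 | 3.8 % | 5.1 % | 87.6 % | 90.1 % |

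Simulation error is about 0.15 points for type I error, √(0.05 × 0.95 / 20,000), and about 0.2 points for power. The gender variance was added to the planning SD: with 102 women among 172 (proportion 0.593), a 12-point difference gives a total SD of √(16.09² + 144 × 0.593 × 0.407) ≈ 17.1. The unadjusted power below 90 % partly reflects that larger total SD and is not a shortfall against the plan's own assumption.

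**4. Limit of these figures.** They describe the t-test branch only. With mean 20 and SD 16.09, a normal distribution would put Φ(−20/16.09) ≈ 11 % of oral-arm values below zero, which is impossible. Skew is therefore plausible, and the Mann-Whitney branch, also unadjusted, could apply. No comparison was computed for it.

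**The case against.** The strongest reply is that nothing here is wrong. Randomisation makes the unadjusted difference unbiased, the trial was sized on the same test, and its standard error already allows for chance baseline imbalance. That stands. A reader might infer an inflated type I error, a biased estimate or an underpowered trial; the documents support none of these. Any departure in type I error is towards conservatism, and precision is lost only relative to a better method.

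Second, the gain may be small. The article gives no gender difference in transferrin saturation; at an assumed 4 points, omitting gender costs practically nothing. Entry restricted to ferritin ≤30 ng/ml and a large repletion dose could both weaken the baseline correlation. This also stands, and it is why the gain is given as a range. Nor can a gender gain be added to the table's figures, since gender and the baseline value may overlap.

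Third, a reader might infer from "non-parametric tests like the Wilcoxon test for related samples" that before-and-after tests within an arm will serve as evidence of treatment effect. The sentence does not say so. It lists that test as a generic option for laboratory results, beside the independent-samples test, and assigns it to no outcome. The primary endpoint and the secondary objectives on haemoglobin and adverse events are worded as comparisons between groups. Extending the model to symptoms is also unsupported: the case report form is described by topic, and no scale is defined.

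Finally, a fuller analysis plan could add covariates. But the article itself names the test, so this is a stated choice and not an omitted detail.

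**Conclusion.** The point holds as an efficiency weakness, not a validity error. The plan fixes an unadjusted comparison while the stratum is known for every participant and a visit-0 blood sample exists for all. The direction of the gain is clear to the extent that these variables predict the outcome; its size is not. At r = 0.2 to 0.3 it is about 1 to 3 power points (90.0 % to 91.1 % or 92.5 %). At r = 0.6 it is about 8 points, and the CI half-width narrows from 4.84 to 3.88. All this rests on a back-solved SD of about 16, an assumed correlation and an outcome near enough to normal for the t-test branch. Visit-0 transferrin saturation is implied by the blood sample and by the mention of a related-samples test, but it is never listed as measured. The change is worth making because it is cheap, not because the present test would mislead.

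**What to change.** By a dated amendment completed before the analysis:

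- Make the primary analysis a linear model of visit-1 transferrin saturation on treatment, visit-0 transferrin saturation and gender, with robust standard errors. Report the adjusted mean difference with its 95 % CI.
- State that transferrin saturation is measured in the visit-0 sample, fresh or stored.
- Keep the unadjusted test as a sensitivity analysis.
- Use the same model, each with its own baseline value, for the other continuous laboratory outcomes.

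A simple change score is not a substitute. With equal variances at both visits its variance is 2(1 − r) times that of the visit-1 value, so it loses precision when r is below 0.5 (1.4 times the variance at r = 0.3).

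The cost is the amendment and one regression in the planned software. No further participants or visits are needed. If transferrin saturation has not yet been measured at visit 0, assays of stored specimens are an added cost, and their availability should be confirmed first.
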